### Intervention

The intervention consists of a five-week inpatient psychosomatic treatment according to an integrative comprehensive concept of depth psychological and cognitive-behavioral therapy. The patients will be admitted in closed groups of 5 to 6 patients each.

All therapists will be physicians in advanced or completed specialized training in psychosomatic medicine and psychologists in advanced or completed training in clinical psychotherapy, physiotherapists, registered nurses, social workers, and psychotherapists for integrative body and movement therapy. At the beginning of the study, all therapists will receive several training courses on psychosomatic aspects of PASC, the PASC guideline, the PASC concept for inpatient psychotherapy, immunological principles of PASC and fatigue, and the treatment of PASC in physiotherapy and aerobic exercise therapy.

We have adopted parts of the concept from the working group of Köllner et al. [44] and adapted it to our psychosomatic inpatient setting. The psychotherapeutic focus of the treatment is on coping with the PASC symptoms and treating comorbid mental symptoms that have arisen as a result of the chronic illness. Table 2 provides an overview of the treatment interventions, addressing the key aims of each element. Four cornerstones of treatment are applied in addition to our regular multimodal, focus-orientated psychotherapy concept. Figure 2 illustrates these cornerstones, which are explained in detail below.

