### Control group

The control group will consist of PASC patients for whom there is an indication for inpatient psychosomatic treatment (depressive symptoms in self-assessment: PHQ-9 ≥ 10), but who do not take up the treatment. After group allocation, participants in the TAU condition will have no access to the inpatient psychosomatic treatment, but will not be restrained from using any form of care for PASC-related symptoms. Treatment as usual for PASC patients can entail follow-up contacts with their treating physician or general practitioner, physical training, occupational therapy, or rehabilitation. At T0, T1, and T2, participants of the control group will be questioned about the received psychotherapeutic inpatient or outpatient treatment.

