**Fig. 2 Fig2:**
[figure not shown]
Four cornerstones of PASC specific inpatient psychosomatic treatment

**Medical treatment** Our comprehensive multidisciplinary medical assessment will include detailed medical examination at the beginning and end of treatment, with evaluations by specialists if new symptoms arise and weekly medical consultations.**Neurocognitive training** Neurocognitive training will be carried out independently with the digital health application NeuroNation MED [45] at least twice a week. The individually customized training plan and the adaptive difficulty level will be tailored to the user’s needs. NeuroNation MED contains over 35 multimodal exercises that target the domains of memory, attention, processing speed, and reasoning. The neurocognitive training will be continued after discharge from inpatient treatment. This is made possible because NeuroNation MED is carried out on a smartphone.**Psychotherapy** Our therapeutic approach is characterized by a permanent validation of the psychological symptoms resulting from a somatic illness, in this case, SARS-CoV-2 infection, acceptance of the status quo and at the same time strengthening self-efficacy and resource orientation. The focus of our psychotherapy concept is on developing an understanding of PASC from a biopsychosocial perspective and learning functional coping skills, taking into account the physical, psychological, and social challenges of PASC. The treatment is based on established, effective methods of cognitive behavioral therapy (CBT) and acceptance and commitment therapy (ACT). To avoid post-exertional malaise (PEM) the focus of psychoeducation is on learning the 3P principle [46], including pacing, planning, and prioritizing. Pacing means, for example, dividing tasks and activities into smaller sections throughout the day and taking breaks. Planning refers to the scheduling of support and the prior provision of aids for activities while prioritizing means setting realistic goals and assessing the importance and necessity of various tasks [2]. To ensure pacing, therapies are individually tailored, meaning patients will be allowed to skip therapies at any time as required or cancel them early. This serves as a training ground for recognizing and setting one’s boundaries.**Physical therapy** will take place in close cooperation and coordination with the Department of Physical and Rehabilitative Medicine at the Universitätsklinikum Erlangen. There will be weekly interdisciplinary meetings to discuss the patient’s current status. The so-called CoFit Training Group (e.g. circuit training, stretching exercises, balance training, breathing therapy, back exercises, etc.) will take place in a group setting twice a week for 30 min each. When indicated, patients will also receive additional pulse-controlled ergometer training in a group setting, depending on their fitness level. Our physiotherapeutic treatment concept for post-COVID will take up established physiotherapeutic treatment approaches for fatigue (e.g. for multiple sclerosis) [33, 34] and will include pacing as a central technique in all therapies. Additionally, patients will rate their symptoms and their exertion rate on the Borg breathlessness scale [47]. This ensures that individual resilience will be taken into account in the CoFit training group and ergometer training and that physiotherapy will continuously be adapted to individual’s progress.

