**Psychotherapeutic interventions**		
PASC psychoeducation group	2x/ week for 90 min	Psychoeducation and development of an individualized disorder model; dealing with PASC, changes in lifestyle and self-esteem; communicating about PASC, coping skills, and psychological mechanisms
Individual psychotherapy	2x/ week for 50 min and 25 min	
Family meeting	1 × 60 min when indicated	Involving the social environment to strengthen social support and give information on PASC
Mindfulness walking group	2x/ week for 30 min	Promoting the recognition of physical limits following the concept of pacing, self-expression, and introspection and reducing distress
Relaxation training group (progressive muscular relaxation and yoga)	2x/ week for 30 min	
Mindfulness training group	2x/ week for 30 min	
Integrative body and movement therapy group	1x/ week for 90 min	Improving patients’ self-awareness and body awareness, helping patients accept their current state, promoting self-efficacy and self-care

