#### Sample size calculation and statistical methods

Sample size calculation was performed with G*Power Version 3.1.9.7 [71, 72]. The sample size calculation is based on testing the primary hypothesis that inpatient psychosomatic treatment leads to a significantly lower mean PCS Score across the first two follow-up assessments (T1 and T2) as compared to treatment as usual. Because of the novelty of PASC, data on our primary outcome, the PCS Score, were not available in this population over different time points. Therefore, we assumed a conservative correlation of 0.5 among repeated measurements and a medium effect size. Based on a medium effect size (f = 0.25) and a power of 85%, a sample size of 98 participants is required, with 49 participants per group. Assuming a conservative dropout of 20%, we will randomize 118 participants, 58 for each condition.

We will perform standard techniques of data preparation with tests of normality and homogeneity and with imputation of missing data in the case of dropouts. Furthermore, we will conduct different descriptive analyses of sociodemographic and medical data. The primary statistical analyses will be a two-way mixed-design Analysis of Variance (ANOVA) with the independent variables being condition (treatment vs. treatment as usual) and time (T0, T1) and condition by time interaction as fixed effects as well as repeated measures ANOVA for the follow-up measurement with repeated measurements. Additionally, we will perform regression analyses to identify potential predictors of treatment outcomes. In all analyses, two-sided p values of < 0.05 are considered to indicate statistical significance. All analyses will be conducted using the statistical software SPSS.

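### Intervention patients are treated in closed groups of 5 to 6, but the ANOVA and sample size treat all patients as independent; if outcomes correlate within groups, standard errors are too small

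*Protocol article*

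**What the plan says.** The Intervention section of the protocol article sets the treatment unit: "The patients will be admitted in closed groups of 5 to 6 patients each". Table 2 lists mainly group sessions, for example "PASC psychoeducation group 2x/ week for 90 min", plus mindfulness walking, relaxation, mindfulness training, body and movement therapy and a weekly group visit. The CoFit training, described with the four cornerstones of treatment, "will take place in a group setting twice a week for 30 min each".

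The Control group section describes care arranged person by person: "Treatment as usual for PASC patients can entail follow-up contacts with their treating physician or general practitioner, physical training, occupational therapy, or rehabilitation". Nothing there groups controls together.

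The section on sample size and statistical methods makes a two-way mixed-design ANOVA on T0 and T1 the primary analysis. Its terms are condition, time and "condition by time interaction as fixed effects", "as well as repeated measures ANOVA for the follow-up measurement with repeated measurements". No term for the closed group appears. The only correlation used in planning is 0.5 among a patient's own repeated measurements. With f = 0.25 and 85% power, the section arrives at 98 patients, 49 per group.

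**The concern.** Patients in one closed group start and finish together and spend most of their treatment time in each other's company. Group dynamics and shared sessions can make their outcomes more alike than those of patients in different groups. A mixed-design or repeated-measures ANOVA handles correlation between visits of the same patient, but not correlation between patients of the same group. Positive within-group correlation makes the mean of the intervention arm less precise than 49 independent patients would give, and the ANOVA does not see this.

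The primary comparison and every between-group secondary comparison would then have p values that are too small and intervals that are too narrow. The stated 85% power would also be optimistic. Recruiting more groups of the same size restores power but does not correct the standard error.

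**Working it through.** **How much treatment is shared.** Regular weekly minutes from Table 2:

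- Group: psychoeducation 180, mindfulness walking 60, relaxation 60, mindfulness training 60, body and movement therapy 90, CoFit 60, group visit 30. Total 540.
- Individual: psychotherapy 75, neurocognitive training 60, medical consultation 20. Total 155.
- Shared fraction: 540/695 = 78%, leaving out once-only and when-indicated items.

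**Number of groups.** The 49 patients to be analysed make 49/6 = 8.2 to 49/5 = 9.8 groups. The 58 to be enrolled make 58/6 = 9.7 to 58/5 = 11.6. That is about 9 to 12 groups.

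**Reproducing the plan's figure.** For the between-groups test in a repeated-measures ANOVA, the noncentrality is λ = f²·N·m/(1 + (m − 1)ρ), with F on 1 and N − 2 degrees of freedom. With f = 0.25, N = 98, m = 3 visits and ρ = 0.5, λ = 0.0625 × 98 × 3/2 = 9.19. Power is 0.851, and 98 is the smallest even N that reaches 85%. The formula has no allowance for groups.

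**Adding one-arm clustering.** The ICC is an assumption, because the documents give none. It refers to the quantity being compared, for example the T0 to T1 change. With average group size k = 5.5:

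- Design effect in the intervention arm: DE = 1 + (k − 1)·ICC. In the control arm it is 1.
- Variance of the arm difference is multiplied by (DE + 1)/2.
- Correct SE over ANOVA SE: √[(DE + 1)/(2 − ICC·(k − 1)/48)]. The small term in the denominator is there because clustering also slightly lowers the variance observed within the arm.
- Power: λ divided by (DE + 1)/2. For example, at ICC 0.05, 9.19/1.1125 = 8.26.

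Type I error was simulated with nine groups (five of 5 and four of 6, total 49) against 49 independent controls, using the ordinary t-test on change scores. With two visits this is the same test as condition by time. There were 40,000 runs per ICC.

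| Assumed ICC | DE | Variance ratio | Correct SE / ANOVA SE | Type I error | Power at N = 98 | N for 85% |
|---|---|---|---|---|---|---|
| 0 | 1.000 | 1.000 | 1.00 | 5.0% | 85.1% | 98 |
| 0.01 | 1.045 | 1.022 | 1.01 | 5.1% | 84.3% | 100 |
| 0.02 | 1.090 | 1.045 | 1.02 | 5.4% | 83.5% | 104 |
| 0.05 | 1.225 | 1.113 | 1.06 | 6.3% | 81.2% | 110 |
| 0.10 | 1.450 | 1.225 | 1.11 | 7.6% | 77.4% | 120 |

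The simulation's standard error is √(0.05 × 0.95/40,000) = 0.1 percentage points. Separate runs at ICC 0.01 gave 5.1%, 5.2% and 5.4%, so about 5.2% is a fair summary there. The power column keeps the plan's 96 denominator degrees of freedom. With only about ten groups the proper degrees of freedom are fewer, so actual power would be a little lower.

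**Which random effect helps.** Write the group effect as u, the same at T0 and T1. In the change T1 − T0 it cancels, so a group intercept constant over time leaves the condition-by-time standard error as it was. In 15 simulated trials with a group effect arising only at T1 (variance 0.10), a repeated-measures model with patient and group intercepts gave an interaction SE averaging 1.00 times the independent-patient SE (range 0.98 to 1.00). The group effect has to act on the contrast itself.

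**The case against.** The strongest objection is that the harm is conditional. A reader might infer from the closed groups alone that the standard errors are too small. The documents do not support that as a fact. They give no ICC; at zero nothing is wrong, and at 0.01 to 0.02 the effect is negligible. Individual psychotherapy, app training done alone, tailoring and the freedom to skip sessions may all keep the correlation low. This stands, and the point is worded accordingly.

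Other stronger readings also fail:

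- A reader might count therapists and season as sources of correlation specific to each group. The Intervention section describes one department's team and does not say that therapists differ between groups. Season affects controls as well.
- A reader might apply the full design effect to the whole trial. Only one arm is clustered, so the variance inflation is (DE + 1)/2.
- A reader might start from the roughly 69% power of a two-sample test of the T0 to T1 change at d = 0.5 and blame the shortfall from 85% on clustering. That gap comes from using a different test. Clustering costs 1 to 9 points on that basis and about 1 to 8 on the protocol's own.

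It can also be said that a condensed article leaves the error structure to an analysis plan that is not shown. This carries less weight here, because the article itself names the model, its terms and the basis of the sample size. Finally, allocation follows patient choice, as the limitations section concedes, and that bias may well exceed an 11% change in a standard error. This is true, but it does not make the standard error right.

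**Conclusion.** The concern holds in conditional form. The article fixes closed groups in one arm, mostly group-delivered treatment, and an analysis and sample size that assume independent patients. For any positive within-group correlation the tests err in the anti-conservative direction.

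The size rests on an assumed ICC of 0.01 to 0.10 and an average group size of 5.5. On that basis the effect runs from trivial to moderate and becomes material from about 0.05, where the type I error is near 6.3% and power near 81%. Without recorded group membership, nobody could later show that the correlation was small.

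**What to change.** Record the closed-group number for every intervention patient, and replace the T1 and T2 analyses with a partially nested linear mixed model, which SPSS MIXED can fit. Either specification below lets the group effect act on the treatment contrast:

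- a model for the T1 (or T2) score adjusted for T0, or for the change score, with a random closed-group intercept in the intervention arm only; or
- the repeated-measures model with a random group-by-time effect in the intervention arm. A group intercept constant over time does not suffice.

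Treat each control as a separate unit, use Satterthwaite degrees of freedom and report the estimated ICC. Restate the 85% power over a stated ICC range. A simplified version (group means against individual controls, Satterthwaite degrees of freedom) held the simulated type I error at 4.8% to 5.1% for ICC 0 to 0.10.

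The cost is one identifier and revised analysis wording; treatment, visits and recruitment procedures stay as they are. The downside is slightly wider intervals and an ICC estimated imprecisely from about 9 to 12 groups. The change does nothing about confounding from self-selection, which needs its own treatment.

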**Fig. 2 Fig2:**
[figure not shown]
Four cornerstones of PASC specific inpatient psychosomatic treatment

**Medical treatment** Our comprehensive multidisciplinary medical assessment will include detailed medical examination at the beginning and end of treatment, with evaluations by specialists if new symptoms arise and weekly medical consultations.**Neurocognitive training** Neurocognitive training will be carried out independently with the digital health application NeuroNation MED [45] at least twice a week. The individually customized training plan and the adaptive difficulty level will be tailored to the user’s needs. NeuroNation MED contains over 35 multimodal exercises that target the domains of memory, attention, processing speed, and reasoning. The neurocognitive training will be continued after discharge from inpatient treatment. This is made possible because NeuroNation MED is carried out on a smartphone.**Psychotherapy** Our therapeutic approach is characterized by a permanent validation of the psychological symptoms resulting from a somatic illness, in this case, SARS-CoV-2 infection, acceptance of the status quo and at the same time strengthening self-efficacy and resource orientation. The focus of our psychotherapy concept is on developing an understanding of PASC from a biopsychosocial perspective and learning functional coping skills, taking into account the physical, psychological, and social challenges of PASC. The treatment is based on established, effective methods of cognitive behavioral therapy (CBT) and acceptance and commitment therapy (ACT). To avoid post-exertional malaise (PEM) the focus of psychoeducation is on learning the 3P principle [46], including pacing, planning, and prioritizing. Pacing means, for example, dividing tasks and activities into smaller sections throughout the day and taking breaks. Planning refers to the scheduling of support and the prior provision of aids for activities while prioritizing means setting realistic goals and assessing the importance and necessity of various tasks [2]. To ensure pacing, therapies are individually tailored, meaning patients will be allowed to skip therapies at any time as required or cancel them early. This serves as a training ground for recognizing and setting one’s boundaries.**Physical therapy** will take place in close cooperation and coordination with the Department of Physical and Rehabilitative Medicine at the Universitätsklinikum Erlangen. There will be weekly interdisciplinary meetings to discuss the patient’s current status. The so-called CoFit Training Group (e.g. circuit training, stretching exercises, balance training, breathing therapy, back exercises, etc.) will take place in a group setting twice a week for 30 min each. When indicated, patients will also receive additional pulse-controlled ergometer training in a group setting, depending on their fitness level. Our physiotherapeutic treatment concept for post-COVID will take up established physiotherapeutic treatment approaches for fatigue (e.g. for multiple sclerosis) [33, 34] and will include pacing as a central technique in all therapies. Additionally, patients will rate their symptoms and their exertion rate on the Borg breathlessness scale [47]. This ensures that individual resilience will be taken into account in the CoFit training group and ergometer training and that physiotherapy will continuously be adapted to individual’s progress.

**Table 2 Tab2:** Overview of the frequency and duration, and key aims of psychosomatic treatment for PASC

	Frequency and duration	Key aims
**Psychotherapeutic interventions**		
PASC psychoeducation group	2x/ week for 90 min	Psychoeducation and development of an individualized disorder model; dealing with PASC, changes in lifestyle and self-esteem; communicating about PASC, coping skills, and psychological mechanisms
Individual psychotherapy	2x/ week for 50 min and 25 min	
Family meeting	1 × 60 min when indicated	Involving the social environment to strengthen social support and give information on PASC
Mindfulness walking group	2x/ week for 30 min	Promoting the recognition of physical limits following the concept of pacing, self-expression, and introspection and reducing distress
Relaxation training group (progressive muscular relaxation and yoga)	2x/ week for 30 min	
Mindfulness training group	2x/ week for 30 min	
Integrative body and movement therapy group	1x/ week for 90 min	Improving patients’ self-awareness and body awareness, helping patients accept their current state, promoting self-efficacy and self-care
**Neurocognitive training**		
Neurocognitive training	2x/ week for 30 min	Improving patients’ neurocognitive impairments by individually tailored exercises on the digital health application NeuroNation MED
**Medical treatment**		
Medical consultation hour	1x/ week for 20 min and when indicated	Addressing medical problems, answering medical questions, if necessary improve adherence to intervention protocols
**Physiotherapy**		
CoFit-Training Group	2x/ week for 30 min	Individualized aerobic exercise training to improve physical and mental resilience, reduce oxidative stress, and exhibit positive effects on immune responses
Individual physiotherapy	When indicated	
Ergometer training group	When indicated	
**Additional elements**		
Social worker	1 × 60 min	Socio-therapeutic counseling on social security issues and work-related problems
PASC group visitation	1x/ week for 30 min	Giving and receiving feedback on the course of treatment, coordination, and adjustment of the treatment plan, if necessary improve adherence to intervention protocols

### Outcomes

#### Primary outcome

The primary outcome are symptoms of PASC at the end of the treatment (T1, see Table 1). To measure those, we will use the PCS-Score. The PCS-Score consists of 12 yes/no questions and covers the entire spectrum of possible PASC symptoms. Each question is given its weighting factor, which assigns a meaning to the corresponding symptom complex. The resulting sum score ranges from 0 (= complete absence of any symptoms) to 59 (= presence of symptoms in each of the 12 symptom complexes). A clinically relevant PASC can be assumed from a PCS Score of 26.25 (high PCS Score). Values between 10.75 and 26.25 indicate an intermediate or moderate PASC. The PCS Score was validated on a German population [48].

